### 7.3.2 Exploratory effectiveness analyses

The exploratory outcomes of mortality, disability, stroke-related hospitalization, and stroke recurrence are binary variables. The modified Poisson GEE approach (with log-link) will be used to obtain risk ratios for binary outcomes, as described above.

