### **3.3 Safety monitoring**

To protect the safety of participants, we designed a multi-level support and supervision system for VDs. Each township and county hospital will have a designated physician on call to provide support to VDs on safe practice. If an event occurs, VDs have to report the event to project coordinator within 12 hours. Death and hospitalization are two main safety monitoring indexes. We will collect data through Nanhe CDC death surveillance system and the county hospital. If

there are significant more death or hospitalization in the intervention group ( $p < 0.10$ ), we will stop the study.

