Data on hospitalization and recurrence of stroke will be collected through extracting the data from county medical insurance system and death record system. Data on hospitalization will be extracted every month from the medical insurance system, which includes the reason and duration of the hospitalization. Death data will be extracted through the death report from the local CDC and verified through a smartphone-based shortened version of verbal autopsy survey administered by county project officer to family members of dead participants in this study. The survey has been proved to be feasible and acceptable in rural north China. Respecting the culturally appropriate grieving period, the interview will be conducted at the sixth and twelfth month after initial of the intervention. **Table 2** shows the overall data collection procedures based on SPIRIT guideline.

803 Table 2. The schedule of enrollment, intervention and assessments

|                                                         | STUDY PERIOD |                     |                              |                                                                                       |       |       |      |       |                      |
|---------------------------------------------------------|--------------|---------------------|------------------------------|---------------------------------------------------------------------------------------|-------|-------|------|-------|----------------------|
|                                                         | Enrollment   | Baseline Assessment | Allocation of treatment arms | Post-allocation                                                                       |       |       |      |       | Close-out Assessment |
| \TIMEPOINT                                              | -3 mon       | -2 mon              | 0 mon                        | 0 mon                                                                                 | 3 mon | 6 mon | 9mon | 12mon | 13 mon               |
| ENROLMENT:                                       |              |                     |                              |                                                                                       |       |       |      |       |                      |

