|                                                                                                |  |   |  |  |   |   |   |  |   |
|------------------------------------------------------------------------------------------------|--|---|--|--|---|---|---|--|---|
| Daily voice messages for participants                                                          |  |   |  |  |   |   |   |  |   |
| OUTCOME ASSESSMENTS:                                                                    |  |   |  |  |   |   |   |  |   |
| Systolic blood pressure                                                                 |  | X |  |  |   |   |   |  | X |
| Mobility                                                                                |  | X |  |  |   |   |   |  | X |
| Medication adherence                                                                    |  | X |  |  |   |   |   |  | X |
| Physical activity level                                                                 |  | X |  |  |   |   |   |  | X |
| Quality of life                                                                         |  | X |  |  |   |   |   |  | X |
| Stroke recurrence                                                                       |  | X |  |  |   |   |   |  | X |
| Hospitalization                                                                         |  | X |  |  |   |   |   |  | X |
| Morbidity and mortality                                                                 |  |   |  |  |   | X |   |  | X |
| Village doctors' knowledge, attitude and practice on the secondary prevention of stroke |  | X |  |  |   |   |   |  | X |
| PROCESS AND ECONOMIC ASSESSMENTS:                                                       |  |   |  |  |   |   |   |  |   |
| Process evaluation                                                                             |  |   |  |  | X | X | X |  | X |
| Cost of intervention                                                                           |  |   |  |  |   |   |   |  | X |

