Exploratory outcomes include stroke recurrence, hospitalization, disability and mortality, which will be collected through questionnaire or medical insurance records. (See **Table 3**) In addition, based on the mortality data we collect, we will conduct a smartphone-based shortened version of verbal autopsy (VA) survey to family members of dead participants in this study, to improve the quality of cause of death data. This survey has been proved to be feasible and acceptable in rural north China by our study team 1. We will use the Population Health Metrics Consortium (PHMRC) Shortened Questionnaire adult module (see **Appendix A-5**, bilingual and adjusted for SINEMA study), which has been validated and elicits sufficient information to diagnose most probable cause of death of public health importance. Trained health workers will conduct the VA interview, which will take about 30 minutes. Respecting the culturally appropriate grieving period, the VA interview will be conducted within 4-12 months after the date of death. An appropriate respondent (usually the family member) must be identified, and informed consent (see **Appendix A-1**) must be obtained before the interview. The trained VA interviewer will conduct the interviews in the local language.

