\*\* Data will be collected through extracting information from medical insurance records.

\*\*\* Data on mortality will be collected through extracting information from death records and verified by a smartphone-based shortened version of verbal autopsy survey.

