#### Exploratory outcomes

|                                              |                                                                                                                                                                                                                                                           |                                                                                                                          |
|----------------------------------------------|-----------------------------------------------------------------------------------------------------------------------------------------------------------------------------------------------------------------------------------------------------------|--------------------------------------------------------------------------------------------------------------------------|
| Stroke recurrence                            | Participants self-reported whether they had experienced stroke events during the 12-months follow-up period.                                                                                                                                              | Binary as experienced a stroke event vs. not experienced a stroke event                                                  |
| Degree of Disability (Modified Rankin Scale) | Participants' degree of disability evaluated based on assessors' observation and participants' self-reported symptoms or disability. A score ranged from 0 (no symptoms) to 5 (severe disability). A score of $\leq 2$ indicates functional independence. | Binary as score 0-1 (no symptoms at all or no significant disability despite symptom) vs (moderate to severe disability) |
| Stroke-related hospitalization               | Participants self-reported whether they were admitted in the hospital due to stroke event.                                                                                                                                                                | Binary as hospitalized due to stroke vs. not hospitalized due to stroke                                                  |

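### Hospitalization is one of two main safety indexes, but the only admission outcome with a planned final comparison by arm is self-reported stroke admission

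*Combined protocol and SAP*

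**What the plan says.** Section 3.3 (Safety monitoring) states "Death and hospitalization are two main safety monitoring indexes" and gives the source: "We will collect data through Nanhe CDC death surveillance system and the county hospital". It names no cause of admission. Its only stated use of the index is to stop the study if the intervention arm has significantly more deaths or hospitalizations at p < 0.10.

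Section 5.6 (Data collection) says: "Data on hospitalization will be extracted every month from the medical insurance system, which includes the reason and duration of the hospitalization". The participant questionnaire in Appendix A-3, given in both arms, asks about any admission in the past 12 months, with days, diagnosis and cost for each. Table 2 schedules a row labelled only "Hospitalization". Section 5.7 says: "Exploratory outcomes include stroke recurrence, hospitalization, disability and mortality, which will be collected through questionnaire or medical insurance records", and then refers to Table 3.

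Table 4 defines one admission outcome, stroke-related hospitalization: "Participants self-reported whether they were admitted in the hospital due to stroke event". It is a yes/no variable in which everyone not admitted for stroke is a no. Section 7.3.2 on exploratory analyses models this outcome alone among admissions: "The exploratory outcomes of mortality, disability, stroke-related hospitalization, and stroke recurrence are binary variables". Mortality, the other safety index, is analysed without restriction by cause.

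**The concern.** The intervention promotes use of antihypertensives, aspirin and statins, and the follow-up record in Appendix A-2 lets village doctors modify prescriptions. That same record lists renal dysfunction, electrolyte imbalance, gum bleeding and rhabdomyolysis as drug effects to ask about. An admission for one of these is a non-stroke admission. Under Table 4 the patient is coded with those never admitted.

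Deaths are compared at the end, and a haemorrhagic stroke would count as a stroke admission. Other serious non-fatal harm has no planned final comparison, although the admissions and their reasons will be in the data.

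The source matters as well. Self-report at the close-out survey gives no value for participants who die or are lost, and some of them may well have been admitted. The insurance extract would not depend on survey completion, but Table 4 does not use it.

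**Working it through.** **Where hospitalization appears in the plan**

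- Section 3.3: safety index, no cause stated, county-hospital source, stopping trigger only.
- Section 5.6: monthly insurance extract with reason and duration. No analysis is attached.
- Table 2 and section 5.7: the unqualified word. Section 5.7 names questionnaire or insurance records as the source.
- Table 3: no hospitalization row. Its participant exploratory rows are stroke recurrence, stroke-related morbidity and stroke-related mortality.
- Table 4 and section 7.3.2: stroke admission only, by self-report.
- Section 5.9: inpatient claims, as costs only.
- Part B, section 3.3.2: stroke-related hospitalization only, although the Part B questionnaire also asks about other admissions.

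None of these plans a final by-arm estimate of all-cause or non-stroke admission.

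**The plan's own figure**

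The only computed figure is the 83% power for SBP in section 5.3. It is used here only to confirm the design inputs. With 23 villages of 24 patients, n = 552 per arm, the design effect is 1 + 23 × 0.04 = 1.92, and effective n = 552/1.92 = 287.5. A 5 mmHg difference with SD 20 then gives 83.4% power by the noncentral t with 44 degrees of freedom (85.0% by the normal approximation). The stated figure reproduces.

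**Precision of the missing estimate**

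Assumptions: 625 per arm (25 villages of 25); equal observed risk p in both arms of 10%, 20% or 30%, because the documents give none; ICC 0.04 from section 5.3, which was set for SBP change, and 0.01 as a lower alternative.

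- Effective n per arm = 625/(1 + 24 × ICC): 625/1.96 = 318.9, or 625/1.24 = 504.0.
- Risk-ratio factor = exp(1.96 × sqrt(2(1 − p)/(p × n_eff))).
- Risk-difference limit = 1.96 × sqrt(2p(1 − p)/n_eff).

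For p = 0.20 and ICC 0.04, the factor is exp(1.96 × sqrt(1.6/63.8)) = 1.36. The risk-difference limit is 1.96 × sqrt(0.32/318.9) = 0.062, and 0.062 × 625 is about 39 patients.

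| Assumed risk | ICC | RR times or divided by | Risk-difference limit | Patients per 625 |
|---|---|---|---|---|
| 10% | 0.04 | 1.59 | 4.7 points | 29 |
| 10% | 0.01 | 1.45 | 3.7 points | 23 |
| 20% | 0.04 | 1.36 | 6.2 points | 39 |
| 20% | 0.01 | 1.28 | 4.9 points | 31 |
| 30% | 0.04 | 1.27 | 7.1 points | 44 |
| 30% | 0.01 | 1.21 | 5.7 points | 35 |

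The factor falls as p rises, because (1 − p)/p falls. All-cause admission includes stroke admission, so at the same n and ICC its risk-ratio interval is no wider than that of the outcome Table 4 keeps.

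The estimate would bound harm rather than settle it. Observed risks of 25% (intervention) and 20% (control) at ICC 0.04 give SE(log RR) = sqrt(0.8/(0.2 × 318.9) + 0.75/(0.25 × 318.9)) = 0.148, so RR 1.25 with 95% CI 0.93 to 1.67.

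**The case against.** The strongest reply is that hospitalization is shorthand for stroke admission in much of this document. Section 5.7 sends the reader to Table 3, whose exploratory rows are stroke-related. Part B lists hospitalization unqualified in its aims and then specifies stroke-related hospitalization, which it describes as in line with the original protocol. Table 2 is a schedule of short labels. This largely stands. A reader might infer that section 5.7 and Table 2 flatly contradict Table 4 on cause, but the documents do not support that. The firm conflict is with section 3.3, where a safety index silently limited to stroke would be a strained reading.

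On source, the Table 3 footnote "Data will be collected through extracting information from medical insurance records" attaches only to stroke recurrence and stroke-related morbidity, so it does not show that insurance records were meant for a general hospitalization outcome. Sections 5.6 and 5.7 do name those records for hospitalization, and Table 4 leaves them out.

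A second reply is that section 7.3 concerns effectiveness, while safety sits in section 3.3 with its own data source and by-arm comparison. That is fair as to where the fix belongs. It does not fill the gap: section 3.3 gives a trigger, with no estimate, interval or final table whether or not it fires.

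A third reply is that monthly visits may prompt referral and raise admissions in the intervention arm, that record completeness is unknown, and that stroke admission is a sensible effectiveness outcome in this trial. All true. These points call for tabulating reasons and for careful wording, but they do not justify having no estimate.

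**Conclusion.** The gap is real and of modest severity. One of two named safety indexes has no planned final estimate, although the data to produce one are already to be collected. At an assumed 20% risk in both arms and 625 per arm, the missing estimate would bound a risk increase at about 6.2 points (39 patients per 625) at ICC 0.04, or 4.9 points (31 per 625) at ICC 0.01. These figures rest on assumed risks, on ICCs not set for admissions, and on full record coverage.

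Three stronger readings are not supported:

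- **A planned result is biased.** No primary, secondary or currently planned exploratory analysis is made invalid by this omission. The point concerns what the trial can say about safety.
- **The interval would exclude an intervention-arm risk above 20% × 1.364 = 27.3%.** That treats the control risk as known. The risk-difference limit above is the right bound.
- **Twelve-month recall misses the first month because Table 2 puts close-out at month 13.** Section 5.6 and the notes to the timeline figure place the assessment at 12 months. At most this is an inconsistency in Table 2.

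**What to change.** Add a safety analysis, either in section 3.3 or as rows labelled safety in Table 4, with a matching sentence or two in section 7.3.2:

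- **Outcomes:** all-cause hospitalization and non-stroke hospitalization within 12 months of allocation, each yes/no, for all enrolled participants.
- **Source:** the monthly insurance extract and the county-hospital safety data. Use Appendix A-3 answers as a supplement for those who complete the survey, and show results with and without them, because A-3 records no admission date. State that admissions of uninsured participants who die or are lost may be missed.
- **Analysis:** the township-adjusted modified Poisson GEE already planned, reporting the risk ratio with 95% CI beside mortality.
- **Interpretation:** tabulate admission reasons by arm. Note that control villages have no SINEMA monthly visits, and that the referral item in the follow-up record (1.3a) covers only cardiovascular, cerebrovascular and related visits, in the intervention arm.

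Keep self-reported stroke admission as the exploratory effectiveness outcome. No new data collection is needed. The costs are coding admission reasons, merging two record sources of unknown completeness, two more exploratory comparisons, and a result that may partly reflect referral.

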## 7.4 Subgroup analyses

To explore the factors related to the effectiveness of the intervention, we will perform subgroup analyses for the following baseline variables: gender (male/female), age group (<65 vs. ≥65), education level (schooling vs. no schooling), years since last stroke events (less than 3 years vs. more than 3 years). These subgroup analyses will be performed by adding to the model both the variable and its interaction term with treatment arm. We caution that these analyses may not be powered.

## 7.5 Strategies to handle missing data in effectiveness analyses

The primary analysis will not use imputation for missing data because a priori, there is no reason to assume that missing data are not missing at random. However, we will identify if there are any baseline covariates related to loss to follow-up by summarizing baseline characteristics and treatment arm by loss to follow-up status. If we identify baseline covariates that are predictive of loss to follow-up, we will adjust for these covariates in the regression models. If loss to follow-up is not negligible, we will also consider implementing the pattern mixture approach to test for sensitivity to missing data assumptions.

## 7.6 Reporting

We will report the study results in a manner consistent with the adaptation of the CONSORT extension reporting guidelines for cluster-randomized controlled trials and web-based and mobile health interventions.

# 8. QUALITY CONTROL AND PROJECT MANAGEMENT

This section will introduce the quality control plan and project management plan.

## 8.1 Project management

The purpose of project management is to conduct interventions and evaluations strictly according to the protocol and the plan. Different levels of managers will be included in the project to take charge of project management at their levels.

### One **Duke Kunshan Project Manager**

- monitor the work of county project officer
- coordinate baseline and evaluation surveys
- communicate with PI, County Project Officer and township managers, and village doctors and village health promoters if necessary
- communicate with county hospital and township hospitals regularly
- deal with emergencies when necessary

### One **County Project Officer**

- monitor the recruitment of village doctors, village health promoters and patients in each village
- coordinate baseline and evaluation surveys
- with the support of APP, monitor the work of village doctors and village health promoters in intervention villages from five towns
- communicate with villages, township hospitals, county hospital and Duke Kunshan managers
- deal with emergencies when necessary

### Five **township managers**

- support the recruitment of village doctors, village health promoters and patients
- coordinate baseline and evaluation surveys
- with the support of APP, monitor the work of five village doctors and five village health promoters in intervention villages of his/her town
- communicate with villages and higher-level managers

In addition, we have International Steering Committee, Policy Advisory Group and Technology Advisory Group which are composed of researchers from different universities and institutes, specialists from hospitals and government officers. Besides, a Community Advisory Group composed of local stakeholders will be established. They will support and give feedbacks on the project management.

## 8.2 Quality control for intervention

The purpose of quality control is to ensure the quality of project implementation throughout the trial; to objectively collect relevant data which will help with data analysis and interpretation; and to provide in-time feedbacks for the optimization of the research design. The quality control will mainly focus on validity, integrity and protocol compliance. Several key measures will be taken:

### **Weekly monitoring via the SINEMA APP**

The SINEMA APP is not only a tool of intervention, but also a tool of quality control. Township managers will be required to monitor the work of village doctors and village health promoters in the intervention group via a build-in module in the APP and submit weekly reports to the county project officer.

#### **Phone-based audit**

Every month, the county project officer will call five randomly selected patients in the intervention group. They will be asked about performances of their village doctors and village health promoters, their medication and rehabilitation. The county project officer is required to send monthly reports to the Duke Kunshan project manager, summarizing the results of the audit.

#### **On-site supervision and audit**

Township managers and county project officer will periodically visit intervention villages during the intervention. The Duke Kunshan project manager or other members of the research will visit the study site every two months to inspect the quality of each steps. For important time points such as recruitment, baseline survey, training, intervention, follow-up surveys, we will visit the site more frequently and stay there for longer time. Records will be made after each site visiting.

